### **5.3 Discontinuation/Withdrawal of Participants from Trial Treatment**

Subjects may be withdrawn from the trial early:

- By withdrawing voluntarily
- On the decision of the Chief Investigator
- On the advice of the LSC

The Chief Investigator may withdraw the subject for any of the following reasons:

- Confirmed pregnancy during the trial
- Any adverse event which results in inability to comply with trial procedures
- Ineligibility either arising during the trial or retrospectively (having been overlooked at screening)
- Significant protocol deviation
- Subject non-compliance with trial requirements
- Loss to follow up (applies to a subject who does not return for protocol trial visits, is not reachable by telephone or other means of communication and/or is not able to be located)

The reason for withdrawal will be recorded in the CRF. Subjects withdrawn from the trial may be replaced on the decision of the Investigator. If the subject is withdrawn due to an AE, the Investigator will arrange for appropriate specialist management or follow up visits or telephone calls until the AE has resolved or stabilised. The extent of follow up after premature discontinuation will be determined by the Investigator but will be at least for the whole trial period, and if pregnant, until pregnancy outcome.

Subjects found during bronchoscopy to have a previously undiagnosed condition thought to require further medical attention will be referred appropriately to their GP or an NHS specialist service for further investigation and treatment. If a volunteer withdraws from the study, blood samples collected before their withdrawal from the trial will be used/ stored unless the volunteer specifically requests otherwise

### **5.4 Vaccination postponement Criteria**

Vaccination will not proceed on the scheduled day in any of the following situations:

- The subject has a current or recent upper respiratory tract infection, unless they have been symptom-free for at least one week
- The subject has a positive pregnancy test
- The subject has a temperature  $> 37.5^{\circ}\text{C}$
- The Investigator judges the subject to have an acute moderate or severe illness (whether febrile or not)
- The subject has received a live non-trial vaccine within the preceding three weeks
- The Investigator has any other concern that vaccination may not be in the subject's best interests

In this case the subject may be vaccinated at a later date or withdrawn from the trial at the discretion of the Investigator.

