## **5.2 Exclusion Criteria**

Subjects must meet none of the following criteria to enter the trial:

- Any respiratory disease, including asthma
- Current smoker
- Clinically significant abnormality on screening chest x-raya
- Clinically significant abnormality of pulmonary function testsa
- Any nasal, pharyngeal, or laryngeal finding which precludes bronchoscopy
- Current use of any medication taken through the nasal or inhaled route including cocaine or other recreational drugs
- Laboratory evidence at screening of latent *M. tb* infection as indicated by a positive ELISPOT response to ESAT6 or CFP10 antigensb
- Clinical, radiological, or laboratory evidence of current active TB diseasea
- Previous vaccination with candidate vaccine MVA85A or candidate vaccine FP85A or any other recombinant MVA vaccine
- Clinically significant history of skin disorder, allergy, atopy, immunodeficiency (including HIV), cancer (except BCC or CIS), cardiovascular disease, gastrointestinal disease, liver disease, renal disease, endocrine disorder, neurological illness, psychiatric disorder, drug or alcohol abuse
- History of serious psychiatric condition
- Concurrent oral or systemic steroid medication or the concurrent use of other immunosuppressive agents
- History of anaphylaxis to vaccination or any allergy likely to be exacerbated by any component of the trial vaccine, sedative drugs, or any local or general anaesthetic agents
- Any abnormality of screening blood or urine tests that is deemed to be clinically significant or that may compromise the safety of the subject in the triala
- Positive HBsAg, HCV or HIV antibodiesa
- Female currently lactating, confirmed pregnancy or intention to become pregnant during trial period
- Use of an investigational medicinal product or non-registered drug, live vaccine, or medical device other than the trial vaccine for 30 days prior to dosing with the trial vaccine, or planned use during the trial period
- Administration of immunoglobulins and/or any blood products within the three months preceding the planned trial vaccination date
- Any other significant disease, disorder, or finding, which, in the opinion of the Investigator, may either put the subject at risk or may influence the result of the trial or may affect the subject's ability to participate in the trial

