## **5.5 Bronchoscopy postponement criteria**

Bronchoscopy will not proceed on the scheduled day in any of the following situations:

- The subject has a temperature  $> 37.5^{\circ}\text{C}$
- The subject has a positive pregnancy test
- The Investigator judges the subject to have an acute moderate or severe illness (whether febrile or not)
- The Investigator has any other concern that bronchoscopy may not be in the subject's best interests

In the event of postponement the bronchoscopy will be rescheduled where possible up to a 3 week window.

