## **8.11 Pregnancy**

Subjects who become pregnant during the trial after the vaccination may continue trial procedures including venepuncture, if appropriate, at the discretion of the Investigator. Subjects who become pregnant before MVA85A vaccination will be withdrawn and will not be vaccinated. Subjects who become pregnant between vaccination and bronchoscopy will not undergo bronchoscopy. The Investigator will collect pregnancy information on any subject who becomes pregnant while participating in this trial. The subject will be followed up to determine the outcome of the pregnancy.

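### Sections 5.2 to 5.5 and 8.11 of the protocol conflict on what follows a positive pregnancy test and on how long after a live vaccine a volunteer may be dosed

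*Protocol*

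**What the plan says.** **Live vaccine.** The exclusion criteria in section 5.2 cover use of a "live vaccine, or medical device other than the trial vaccine for 30 days prior to dosing with the trial vaccine", and the same criterion bars planned use during the trial. Section 5.4, the list applied on the day of vaccination, stops dosing on a shorter interval: "The subject has received a live non-trial vaccine within the preceding three weeks".

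**Pregnancy and vaccination.** Section 5.4 also lists a positive pregnancy test as a reason not to vaccinate that day. The consequence is shared by the whole list: "In this case the subject may be vaccinated at a later date or withdrawn from the trial at the discretion of the Investigator". Section 5.3 names "Confirmed pregnancy during the trial" among the reasons for which the Chief Investigator may, not must, withdraw a subject. Section 8.11 is mandatory: "Subjects who become pregnant before MVA85A vaccination will be withdrawn and will not be vaccinated". Another sentence of 8.11 lets those who become pregnant after the vaccination stay in trial procedures if the investigator judges it appropriate.

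**Pregnancy and bronchoscopy.** Section 5.5 lists a positive test as a reason for postponement and continues: "In the event of postponement the bronchoscopy will be rescheduled where possible up to a 3 week window". Section 8.11 says: "Subjects who become pregnant between vaccination and bronchoscopy will not undergo bronchoscopy".

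**When the checks happen.** Table 1 schedules urine pregnancy tests at screening and on days 0, 7, 28 and 35. Vaccinations are on days 0 and 28, bronchoscopies on days 7 and 35. Inclusion and exclusion criteria are ticked at screening only. A contra-indication check is ticked at screening and on days 0, 7, 28 and 35. Section 7.3 adds a review of continuing eligibility on the day of enrolment, which is the day 0 vaccination visit.

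**The concern.** Sections 5.4 and 5.5 are the lists that staff use on vaccination and bronchoscopy days. On two matters they lead to a different outcome from another section of the same protocol, and no section is given precedence. An operator who defers a volunteer under 5.4 or rebooks under 5.5 complies with that section and departs from 8.11. An operator who doses a volunteer 25 days after a live vaccine complies with 5.4 and departs from 5.2.

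At stake are consistent handling of volunteers receiving an unlicensed recombinant vaccine and sedated bronchoscopy, avoidable protocol deviations, and withdrawals that depend on which page was consulted. The last matters a little for the data too: section 5.3 allows withdrawn subjects to be replaced, so inconsistent withdrawal also means inconsistent membership of arms of 12.

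**Working it through.** The protocol states no figure to reproduce. The check is day arithmetic and a side-by-side reading.

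**Step 1: the live-vaccine intervals.** Inputs: 30 days (5.2) and three weeks (5.4).

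- Three weeks = 3 × 7 = 21 days.
- 5.4 stops dosing on days 1 to 21 after a live vaccine; 5.2 rules it out on days 1 to 30.
- Conflict: days 22 to 30, that is 30 − 21 = 9 days.

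**Step 2: where a check closes that gap.** At day 0, section 7.3 has eligibility reviewed again, so 5.2 applies alongside 5.4. At day 28, Table 1 has only the contra-indication check, so the gap stays open.

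For a boost on day *b*, the conflicting live vaccine was given between day *b* − 30 and day *b* − 22:

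- *b* = 28 (nominal): day −2 to day 6.
- *b* = 23 (28 − 5): day −7 to day 1.
- *b* = 33 (28 + 5): day 3 to day 11.

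The ±5 window therefore spans day −7 to day 11. This takes the window around nominal day 28. Table 1 in fact counts windows from the previous actual visit, so the dates can shift further. A live vaccine given on days −7 to −1 would already have stopped a day 0 prime under both sections. What remains in practice is one given from day 0 onwards, to day 6 on the nominal schedule or day 11 at the end of the window.

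**Step 3: a positive pregnancy test, visit by visit.**

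| Visit | Sections 5.3 to 5.5 | Section 8.11 |
|---|---|---|
| Day 0, first vaccination | Not that day; then later vaccination or withdrawal, by judgement | Withdrawal, no vaccination |
| Day 7, first bronchoscopy | Not that day; rebook if possible, within 3 weeks | No bronchoscopy |
| Day 28, second vaccination | As day 0 | Two clauses apply (Step 4) |
| Day 35, second bronchoscopy | As day 7 | No bronchoscopy |

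**Step 4: day 28.** Section 8.11 speaks of vaccination as a single event, but the schedule has two. A volunteer first testing positive on day 28 has become pregnant after the first dose, so she may continue procedures by judgement. She is also pregnant before the second MVA85A dose, so she is to be withdrawn and not vaccinated. Both clauses fit. For group 2 volunteers who receive only saline on day 28 under the change in section 4.1, the second clause has no remaining MVA85A dose to refer to, which makes the wording fit less well still.

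**Step 5: does any route lead to the procedure while the test is positive?** No. Sections 5.4 and 5.5 both open by stopping the procedure. On the natural reading, a rebooked visit meets the same list, and a volunteer still testing positive is stopped again. The contradiction is confined to what follows the positive result.

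**The case against.** The strongest reply is that the sections can be read together. Section 5.4 has one closing sentence for six situations and offers deferral or withdrawal; section 8.11, being specific to pregnancy, could be taken to say which applies. Section 5.5 says only that rebooking happens where possible. The triggers also differ: 5.4 and 5.5 act on a positive test, 5.2 and 5.3 on confirmed pregnancy, and 8.11 on becoming pregnant. Pausing on an unconfirmed test and withdrawing on a confirmed pregnancy would be compatible steps. This is a plausible intention, but the protocol describes no confirmation step and gives no order of precedence, and the reading does not settle day 28.

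On live vaccines, 5.2 governs entry and 5.4 governs the day, so passing 5.4 does not waive 5.2. Section 7.3 applies both at day 0, and planned live vaccines are barred throughout. All of this stands, and it narrows the conflict mainly to an unplanned live vaccine before the boost. It does not remove it: the 5.2 interval is counted back from dosing, which can be read as covering the second dose. Section 5.3 makes ineligibility arising during the trial a matter for discretion.

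A reader might infer more: that the protocol permits a pregnant volunteer to be dosed or to undergo bronchoscopy. It does not (Step 5). Nor is there support for two sites diverging. The trial has one vaccine centre and one respiratory centre in Oxford, and any divergence would be between operators. Finally, nothing in the protocol indicates how many volunteers would be affected, or that a live vaccine 22 to 30 days earlier changes the readouts.

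**Conclusion.** The contradictions stand in the current text.

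- **Live vaccine:** 9 days (22 to 30) under opposite rules, largely contained at day 0 and open at the day 28 boost. This assumes that both intervals are counted in whole days back from dosing and that the 5.2 interval applies to the boost.
- **Pregnancy:** at each of the four scheduled tests after screening, section 8.11 and sections 5.3 to 5.5 differ on what follows, and on day 28 section 8.11 also gives two answers.

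The effect on the statistical results is small. One volunteer would be 1/12 = 8.3% of an arm, but that is arithmetic on a hypothetical case, since the protocol gives no expected frequency. The point is inconsistent safety instructions and avoidable deviations. It is not a claim of permitted exposure in pregnancy or of a biased comparison.

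**What to change.** The sponsor should reconcile sections 5.2, 5.3, 5.4, 5.5 and 8.11 as follows.

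1. State the consequence of a positive pregnancy test consistently for each vaccination (days 0 and 28) and each bronchoscopy (days 7 and 35), including expressly the interval between the two vaccinations. If an unconfirmed test and a confirmed pregnancy are meant to lead to different steps, say so.
2. Either make the live-vaccine rules in 5.2 and 5.4 agree, or state expressly which rule governs entry and which governs each vaccination.
3. Add cross-references so that the lists in 5.4 and 5.5 point to the governing rule.

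Which rule and which interval is right, and whether entry and boost should share one, is for the sponsor to decide. The cost is wording in five sections and the matching visit checklists, with no added procedures and no change to sample size or analysis.

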## **5.5 Bronchoscopy postponement criteria**

Bronchoscopy will not proceed on the scheduled day in any of the following situations:

- The subject has a temperature  $> 37.5^{\circ}\text{C}$
- The subject has a positive pregnancy test
- The Investigator judges the subject to have an acute moderate or severe illness (whether febrile or not)
- The Investigator has any other concern that bronchoscopy may not be in the subject's best interests

In the event of postponement the bronchoscopy will be rescheduled where possible up to a 3 week window.

## **6 TRIAL VACCINE, MEDICINES & DEVICES**

### **6.1 Candidate TB vaccine MVA85A**

#### **Description**

The MVA85A vaccine consists of the attenuated vaccinia virus MVA vector with a 1176 base-pair insert, which is almost the complete *M. tb* gene for Ag85A, with the tissue plasminogen activator (TPA) signal sequence preceding the N terminus and a monoclonal antibody tag (pk) at the C terminus. Expression of the antigen 85A DNA sequence is regulated by the vaccinia P7.5 early/late promoter. MVA85A is manufactured under Good Manufacturing Practice conditions by IDT Biologika GmbH (IDT), Germany.

#### **Formulation**

MVA85A lot 0050811 is supplied as a sterile liquid in glass vials. Each vial contains 400  $\mu\text{L}$  of vaccine at a concentration of  $8.4 \times 10^8$  pfu/mL in 10mM Tris buffer 140 mM NaCl, pH 7.7. The dose of MVA85A to be used in this trial will be  $5 \times 10^7$  pfu (60  $\mu\text{L}$ ) in a single intradermal injection into the deltoid region of the upper arm or diluted in saline and administered by aerosol administration. Therefore two doses may be obtained from a single vial, enabling two volunteers to be vaccinated within the same time period.

#### **Vaccine Supply and Product storage**

MVA85A will be shipped from IDT directly to the Clinical Biomanufacturing Facility (CBF) on dry ice and in the presence of a temperature logger. The vaccine will be certified and labelled for use in trial TB035 by a qualified person (QP) at the University of Oxford.

The vaccine will be stored between  $-70^{\circ}\text{C}$  and  $-90^{\circ}\text{C}$ , in a locked freezer, at the University of Oxford, Churchill Hospital

#### **Dispensing and administration**

All movements of vials of the trial vaccine between IDT and the University of Oxford and in or out of the locked freezer will be documented. Vaccine accountability, storage, shipment and handling will be in accordance with local SOPs and other relevant local forms. On vaccination day, vaccines will be allowed to thaw to room temperature and will be administered within 1 hour. The vaccine will be administered intradermally over the deltoid region of each upper arm, according to the site-specific SOP. The vaccine will administered by aerosol inhalation according to the site-specific SOP. Subjects will stay in the unit for 60 minutes ( $\pm 10$  minutes) after vaccination. During the administration of the

vaccine, monitoring equipment, oxygen, medicines including bronchodilators and resuscitation equipment will be immediately available for the management of anaphylaxis and bronchospasm according to the site SOP.

In order to minimise dissemination of the recombinant vectored vaccine virus into the environment, a number of measures will be instituted during and following vaccination:

- The intradermal injection site will be covered with a dressing after vaccination to absorb any virus that may leak out through the needle track. The dressing will be removed from the injection site after 30 minutes.
- The aerosol inhaled vaccination will take place in a closed clinic room and not opened until 10 minutes after the end of nebulisation.
- The dilution process will be carried out in a sealed vial in accordance with the site-specific SOP.
- During aerosol inhalation the Investigator will wear appropriate protective clothing as agreed with the GMSC.
- All disposable items including nebuliser parts, needles, vials, dressings, and protective clothing will be disposed of as GMO waste by autoclaving, in accordance with the current approved SOPs and standard UK practice.
- The hard surfaces within close range (1-2 metres) of aerosol vaccination will be cleaned and disinfected in accordance with GMSC recommendations.
- Non-disposable parts of the MicroAIR NE-U22 nebuliser will be cleaned and disinfected in accordance with the device documentation and GMSC recommendations.

### **Trial regimen**

Group 1: Aerosol inhaled MVA85A  $5 \times 10^7$  pfu (and intradermal saline placebo) on day 0, followed by homologous boosting with MVA85A  $5 \times 10^7$  pfu intradermal on day 28 (and aerosol inhaled saline placebo)

Group 2: Intradermal MVA85A  $5 \times 10^7$  pfu (and aerosol inhaled saline placebo) on day 0, followed by homologous boosting with MVA85A  $5 \times 10^7$  pfu aerosol inhaled on day 28 (and intradermal saline placebo) OR, following safety amendment (see section 4.1)

Intradermal MVA85A  $5 \times 10^7$  pfu (and aerosol inhaled saline placebo) on day 0, followed by aerosol inhaled saline placebo and intradermal saline placebo on day 28

Group3: Intradermal MVA85A  $5 \times 10^7$  pfu (and aerosol inhaled saline placebo) on day 0, followed by homologous boosting with MVA85A  $5 \times 10^7$  pfu intradermal on day 28 (and aerosol inhaled saline placebo)

### **Labelling and packaging**

The vaccine, including intended route of administration, will be QP certified and labelled with Annex 13 compliant labels for trial TB035 at the CBF. The vials will be packaged into labelled cardboard boxes at the CBF.

## **6.2 Saline**

Sterile saline (0.9%) will be used for dilution and placebo doses. The volume of saline used as placebo will be identical to the vaccine volume by the same route. For volunteers receiving the aerosol vaccination we will administer  $5 \times 10^7$  pfu of vaccine made up to 1ml with saline and at the same time a paired placebo of 135 microlitres of normal saline for intradermal injection. For volunteers receiving the vaccine intradermally we will administer  $5 \times 10^7$  pfu of vaccine made up with normal saline to a vaccine volume of 135 microlitres and at the same time a paired placebo of 1ml of saline inhaled. We require 60ul of MVA85A vaccine to give a dose of  $5 \times 10^7$  pfu. For the aerosol vaccine the total volume is 1ml, i.e. ~940 microlitres of saline and 60 microlitres of vaccine. The volume for intradermal injection is 135 microlitres, i.e. ~75 microlitres of saline with 60microlitres of vaccine.

### **6.3 MicroAIR NE-U22**

This is an approved electromedical device, CE0197, EAN code 40 15672 10142 1. Information about the specifications, usage, and maintenance of the nebuliser device can be found in the device documentation (66). This is the same device used for the study TB026.

### **6.4 Sedative & anaesthetic agents for bronchoscopy**

Fentanyl is a licensed opioid used routinely to provide analgesia and sedation during medical procedures. It will be stored, dispensed and administered in accordance with standard NHS procedures and the Summary of Product Characteristics (SmPC).

Midazolam is a licensed benzodiazepine used routinely to provide sedation and amnesia during medical procedures. It will be stored, dispensed and administered in accordance with standard NHS procedures and the Summary of Product Characteristics (SmPC).

Lignocaine is a licensed local anaesthetic used routinely during medical procedures. It will be stored, dispensed and administered in accordance with standard NHS procedures and the Summary of Product Characteristics (SmPC).

Other licensed drugs may be used during bronchoscopy at the discretion of the Investigators.

## **7 TRIAL SCHEDULE**

### **7.1 Recruitment**

Subjects may be recruited by use of an advertisement formally approved by the ethics committee and distributed or posted in the following places:

- In public places (including NHS hospitals and university buildings) with the agreement of the owner or proprietor
- In newspapers or other literature for circulation
- On radio via announcements
- On a website operated by our group or with the agreement of the owner or operator
- As a post on a Twitter account owned and operated by our group
- By e-mail distribution to a group or list only with the express agreement of the network administrator or with equivalent authorization
- On stalls or stands at exhibitions or fairs
- Via presentations (e.g. presentations at lectures or invited seminars)
- Direct mail-out. This will involve obtaining names and addresses of adults via the most recent Electoral Roll (with the contact details of individuals who have indicated that they do not wish to receive postal mail-shots already removed). The company providing this service is registered under the Data Protection Act 1998. Investigators would not be given dates of birth or ages of individuals but the list supplied would only contain names of those aged between 18-55 years (as per the inclusion criteria).

- Oxford Vaccine Centre databases: We may contact individuals from databases of groups within the CCVTM, (including the Oxford Vaccine Centre database) of previous trial participants who have expressed an interest in receiving information about all future studies for which they may be eligible.

A copy of intended advertising will be submitted with the initial application for ethical approval and any significant changes to this advert will be submitted as an amendment to the ethics committee for approval before use.

